## Abstract

**Background:**

Cognitions and perceptions of workers with chronic health problems, such as catastrophizing thoughts and fear-avoidance beliefs, can negatively influence work participation. The Progressive Goal Attainment Program (PGAP) is an intervention developed in Canada with the aim of decreasing limiting cognitions and perceptions and increasing work participation. The objective of this protocol article is to describe the design of a randomized controlled superiority trial to study whether PGAP is effective in decreasing limiting cognitions and perceptions and increasing workability and work participation of workers with chronic health problems in the Netherlands.

**Methods:**

This study is a randomized controlled superiority trial with two (parallel) groups, in which workers on sick leave are randomly assigned to an intervention group (PGAP intervention) or to a waiting-list control group (care as usual). The PGAP intervention consists of a maximum of 10 weekly individual sessions provided by a trained PGAP professional in which the worker learns about staying active, planning activities, and setting goals. Participants in this risk-targeted behavioral activation intervention also learn to be more aware of their cognitions and perceptions and learn about solution-focused problem-solving skills in challenging situations. The primary outcome is the degree of catastrophizing. Secondary outcomes are other personal cognitions and perceptions (e.g., expectations regarding return to work, self-efficacy), health symptoms (e.g., fatigue, depression), work participation (e.g., sick leave status, work hours), and other work-related outcomes (e.g., workability, quality of working life).

**Discussion:**

Although PGAP shows positive effects in Canada, we do not know whether this intervention is effective in the Netherlands. This study is the first randomized controlled trial to test the effect of PGAP on limiting cognitions and perceptions and on work participation of workers with chronic health problems in the Netherlands. If PGAP is effective it could be implemented in the Netherlands in order to stimulate workability and work participation of workers.

**Trial registration:**

The protocol of this study is registered in the Netherlands Trial Register (NL9832) in October 2021.

**Supplementary Information:**

The online version contains supplementary material available at 10.1186/s13063-022-06698-8.

## Background

Because of better treatments, an increase in life expectancy, and the increased retirement age, the number of people of working age with chronic health problems is rising [1–3]. Having chronic health problems can have a negative impact on workability and return to work (RTW) after sick leave [4–6]. Important factors that can influence work participation of workers with chronic health problems are cognitions and perceptions of workers, such as catastrophizing thoughts and fear-avoidance beliefs [7]. Results of previous studies show that catastrophizing thoughts can lead to delayed recovery, an increase in the duration of work absence, work disability, and functional limitations [7–10].

In a scoping review, interventions were identified that were aimed at changing cognitions and perceptions and increasing work participation [11]. The Progressive Goal Attainment Program (PGAP) is a promising intervention with the aim to decrease limiting cognitions and perceptions and to increase work participation [12, 13]. This risk-targeted behavioral activation intervention, which consists of a maximum of 10 sessions, focuses on important cognitions and perceptions, such as fear-avoidance beliefs, catastrophizing thoughts, RTW expectations, or self-efficacy. PGAP is aimed at different groups of patients, i.e. patients with pain, depression, posttraumatic stress disorder, cancer, and other chronic health problems. The intervention can be provided by different occupational health (OH) professionals, such as occupational physicians (OPs) or OH practitioners, after completing a short training program [13].

Studies show positive effects of PGAP on decreasing catastrophizing thoughts, decreasing fear-avoidance beliefs, and increasing RTW in Canada [14–16]. The intervention is so far implemented in other countries such as the USA [17], Australia [18], Ireland [19], and South Africa [20] in which positive effects of PGAP were demonstrated. In the USA, participation in PGAP increased the activity of participants, reduced fear, and improved the ability to pursue goals [17]. In South Africa, participation in PGAP increased self-efficacy and decreased pain catastrophizing and fear-avoidance beliefs [20]. In Australia, participation in PGAP resulted in a reduction of depressive symptoms and fatigue symptoms [18].

Because the empirically supported effects of PGAP are positive, it is aimed at a broad group of patients and it can be provided by different OH professionals, PGAP is a promising intervention to change cognitions and perceptions and improve work participation. However, it is unknown whether PGAP is effective in the Dutch context in changing cognitions and perceptions and stimulating work participation. Because occupational healthcare differs across countries, it may be possible that the effect of PGAP in comparison to care as usual in the Netherlands differs from other countries that studied the effects of PGAP [21]. Besides, although different studies demonstrate positive effects of PGAP, the effects of PGAP are not studied among workers with different chronic health problems in a randomized controlled trial yet. Therefore the objective of this protocol article is to describe the design of a randomized controlled superiority trial with two parallel groups to study whether PGAP (1) is effective in decreasing limiting cognitions and perceptions and (2) is effective in increasing workability and work participation of workers with chronic health problems in the Netherlands. We hypothesize that participants who participate in PGAP score lower on limiting cognitions and perceptions, such as catastrophizing, fear-avoidance, perceived injustice, and perceived disability than participants who do not participate in PGAP. We also hypothesize that participants who participate in PGAP score higher in work ability, have a higher chance to RTW and have more working hours than participants who do not participate in PGAP.

## Methods

The Medical Ethics Review Committee of the Amsterdam UMC – location Academic Medical Center, University of Amsterdam, approved the randomized controlled trial described in this protocol (2021_231). All procedures performed in the trial involving human participants will be in accordance with the ethical standards of the institutional and/or national research committee and with the 1964 Helsinki declaration and its later amendments or comparable ethical standards. The trial is registered in the Netherlands Trial Register (NL9832). This study protocol is written in accordance to the Standard Protocol Items: Recommendations for Interventional Trials (SPIRIT) guidelines (Additional file 1) [22].

### Study setting

This project was initiated by the Department of Public and Occupational Health, Coronel Institute of Occupational Health of the Amsterdam UMC location University of Amsterdam, which is located in the Netherlands. The Netherlands has about 17,4 million inhabitants. The participants will be recruited by OPs and OH practitioners from a national occupational health service (OHS), which has multiple branches spread over the Netherlands. The core business of the OHS is to offer services to different organizations with the goal to increase the health of workers, promote sustainable employability, prevent sick leave, and offer support for RTW after sick leave. The task of the OP in the Netherlands is to prevent work-related diseases and to support workability and RTW after sick leave. The OH practitioner collaborates with the OP and works in task delegation of the OP to reduce the work pressure of the OP. Both OPs and OH practitioners have consultations with workers to promote workplace health, to prevent sick leave, or to support RTW. Six OH practitioners from the OHS will also be the PGAP providers (“coaches”) in this study. The six OH practitioners were selected by the director of the OHS (HZ) by convenience sampling. The OH practitioners were eligible to become a PGAP coach if they could understand and speak Dutch and English.

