### Recruitment procedure

Participants will be recruited by OPs and OH practitioners from a large national OHS in the Netherlands. The OP or OH practitioner assesses whether the worker is possibly eligible for participation. The OP or OH practitioner assesses (1) whether the worker is on long-term or frequent sick leave, (2) whether he or she experiences functional limitations associated with his or her mental or physical complaints, and (3) whether the worker possibly has cognitions or perceptions that may limit workability or work participation. When the OP or OH practitioner thinks PGAP is a suitable intervention for the worker, he or she asks if the worker is interested in participating in the PGAP project. The OP or OH practitioner gives the participant a leaflet with information about the project. If the worker is interested and gives permission, the OP or OH practitioner will send the contact details of the worker to the researchers. Next, the researchers send the worker the information letter about the PGAP project and an informed consent form. Workers will also be able to ask questions about the PGAP project during an online meeting with one of the researchers and will watch an introduction video about PGAP. If the worker is not interested in participation, the OP or OH practitioner asks whether the worker wants to provide the reason for this, but the worker is not obliged to provide a reason. When the worker is interested, has signed the informed consent form, and has sent it to the researcher, he or she receives the first screening questionnaire which can be completed online. With the screening questionnaire, we will assess whether the worker really has limiting cognitions and perceptions. Only then, the worker meets the inclusion criteria and can participate in PGAP. The screening questionnaire will also be used as the T0 measurement.

In order to motivate workers to participate in this study and to remain participants throughout the study, all participants will have the opportunity to participate in PGAP without costs and all participants will receive a gift card of 20 euros after finishing the study.

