The participants in the control group will receive care as usual, which could differ between the participants depending on their health issues and duration of sick leave. After the participants in the control group complete the final assessment, they will have the opportunity to participate in PGAP. The participants in both the intervention and control groups are allowed to participate in other interventions or care during the trial. Whether they participate in other types of care will be assessed in the questionnaires.

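### Six OH practitioners of the recruiting service are also the PGAP coaches, and nothing stated keeps a coach from remaining a control participant's usual practitioner before T3, so PGAP techniques may reach controls and dilute the contrast

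*Protocol article*

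**What the plan says.** Four statements in the protocol article bear on the point.

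- **Coaches.** Study setting: "Six OH practitioners from the OHS will also be the PGAP providers". They were chosen by convenience sampling, and the only condition given is language: "The OH practitioners were eligible to become a PGAP coach if they could understand and speak Dutch and English". The Intervention section describes their training: nine webinars, a two-day skills workshop and an exam.
- **Usual practitioners.** Study setting, on the same professional group: "Both OPs and OH practitioners have consultations with workers to promote workplace health, to prevent sick leave, or to support RTW".
- **Recruiters.** Recruitment procedure: "Participants will be recruited by OPs and OH practitioners from a large national OHS in the Netherlands". The invitation follows the recruiter's own judgement: "When the OP or OH practitioner thinks PGAP is a suitable intervention for the worker".
- **Control arm.** Intervention: "The participants in the control group will receive care as usual, which could differ between the participants". The same section adds "The participants in both the intervention and control groups are allowed to participate in other interventions or care during the trial" and says that use of other care will be asked about in the questionnaires. The one timing rule is "After the participants in the control group complete the final assessment, they will have the opportunity to participate in PGAP". Data collection and management puts the last assessment, T3, at 22 weeks after screening.

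Allocation randomises individual participants 1:1 and states that OPs, coaches and participants are not blinded. Strengths and limitations lists lack of blinding, mixed health problems, a single service and short follow-up. It does not list contamination.

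**The concern.** The same group of staff fills three roles: recruiter, usual-care practitioner and PGAP coach. Because individual workers are randomised, a coach may recruit a worker from his or her own caseload, see that worker allocated to control, and go on holding return-to-work consultations with that worker until T3. The coach would know the allocation and would be newly trained in activity planning, goal setting and thought monitoring.

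The trial question is PGAP against Dutch care as usual. Any PGAP technique used in a control's ordinary consultations moves the control mean toward the PGAP mean. This shrinks the difference in catastrophizing and, potentially, in the work outcomes. The recording described may miss it. The coach checklist is completed after PGAP sessions, and a control asked about other types of care may not count something done within a routine occupational-health consultation. Contamination that goes unrecorded cannot be examined at the analysis stage.

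**Working it through.** **Step 1. Do the documents close the route?**

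| Link in the route | What the article states | Closed? |
|---|---|---|
| A coach recruits from own caseload | OH practitioners recruit; coaches are OH practitioners of the same service; no exclusion | No |
| That worker is allocated to control | Individual 1:1 randomisation | No |
| The coach continues as usual practitioner to T3 | Return-to-work consultations are normal OH practitioner work; no rule on controls | No |
| Formal PGAP is given to the control | Only after the final assessment | Yes |
| PGAP techniques are used in ordinary consultations | Care as usual is not fixed in content | No |
| Exposure is recorded | Other care is asked about; contact with a coach is not named | In part |

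The design as stated permits the route. It does not show that anyone takes it.

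**Step 2. Reproduce the plan's sample size.** Inputs from Sample size: difference 2.4, SD 3.0, significance level 0.05, 15% loss, 25 per group needed, 30 per group randomised. Two assumptions: the 0.80 printed there as alpha is the power, and the test is two-sided.

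- n per group = 2 × (1.96 + 0.84)² × 3.0² / 2.4² = 24.5, so 25.
- 25 / 0.85 = 29.4, so 30 per group and 60 in total.

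The plan's figure reproduces. It allows for dropout and not for dilution. By the exact t-test, 25 per group gives power 0.791, so there is no reserve.

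**Step 3. Effect of dilution.** Let f be the share of controls seen by a coach and e the fraction of the PGAP effect passed on. Neither is in the documents, so both are assumptions. The expected difference is 2.4 × (1 − f × e). Power is from the two-sample t-test with 25 per arm, two-sided 0.05. Its noncentrality is difference / (SD × √(2/25)), which without dilution is 2.4 / 0.849 = 2.83.

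The Statistical analyses section plans a model with baseline catastrophizing as covariate. To approximate this, the SD is multiplied by √(1 − r²), where r is an assumed correlation between baseline and follow-up: 2.86 at r = 0.3 and 2.60 at r = 0.5.

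| f × e | Difference | Power, unadjusted | Power, r = 0.3 | Power, r = 0.5 |
|---|---|---|---|---|
| 0 | 2.40 | 0.79 | 0.83 | 0.89 |
| 0.05 | 2.28 | 0.75 | 0.79 | 0.86 |
| 0.10 | 2.16 | 0.70 | 0.74 | 0.82 |
| 0.20 | 1.92 | 0.60 | 0.64 | 0.73 |

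To hold 80% power by the method of Step 2 (unadjusted, 15% loss), the number to randomise per arm would be 33, 37 and 46 at dilution 0.05, 0.10 and 0.20, against 30 planned.

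**Step 4. What the dilution values mean.** With 30 controls, f = 0.20 is 6 controls seen by a coach; with e = 0.25, f × e = 0.05. Reaching 0.20 takes, for example, f = 0.40 (12 controls) and e = 0.50.

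**The case against.** The strongest reply is that this argues from silence. The article condenses a fuller protocol, and a rule on coach caseloads could sit there. It may. But the article itself makes the coaches members of the recruiting staff and describes recruitment, allocation and control care with no separation. If a rule exists, one sentence settles the matter.

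Second, contamination needs several steps in a row, and none is documented. The article does not say that the six keep an ordinary caseload during the trial, or how often a worker is seen. Six coaches in a national service with several branches, with OPs also recruiting, may overlap with few controls. PGAP is up to ten one-hour sessions with a workbook, so ordinary consultations are unlikely to pass on most of its effect. This stands. It is why the size is only an assumed range, and why the higher values need demanding assumptions.

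Third, the unadjusted t-test understates the planned analysis. This also stands. At r = 0.5, power is 0.82 even with 10% dilution.

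Fourth, there are partial safeguards: formal PGAP is withheld from controls until after the final assessment, and other care is recorded. They narrow the gap without closing it.

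A reader might also infer that a coach who handles a participant's sick-leave case confounds the PGAP arm. The documents do not support this. Occupational-health professionals are the intended providers, and discussing return to work with the worker is part of the programme.

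**Conclusion.** The point holds as a design weakness: the stated roles allow PGAP techniques to reach controls before T3, no stated rule prevents it, and the direction of the resulting bias is toward no difference. If 5% to 20% dilution is assumed, the difference falls from 2.4 to between 2.28 and 1.92, and unadjusted power falls from 0.79 to between 0.75 and 0.60. At r = 0.5 the fall is from 0.89 to between 0.86 and 0.73. These figures rest on assumed f, e and r.

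A reader might infer that controls will receive PGAP, or that a null result would be uninterpretable. The documents support neither. Overlap is possible, its frequency is unknown, and it may be small. Nor do they support requiring that the sick-leave cases of affected workers pass to another practitioner until T3. That would alter the usual care being compared for 22 weeks, and the documents give no staffing figures from which to judge its cost.

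**What to change.** 1. In Study setting and Recruitment procedure, state that workers on the six coaches' own caseloads are not recruited, so that participants come from the caseloads of OPs and other OH practitioners.
2. Add one item to the existing other-care questions at T1, T2 and T3: whether a control participant had a consultation with one of the six coaches.
3. Run a sensitivity analysis on this item, with the intention-to-treat comparison kept as primary. Contact with a coach arises after randomisation, so the analysis shows how far the result could depend on contamination and does not replace the main estimate.
4. Name contamination as a limitation in Strengths and limitations.

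Cost: protocol wording, one questionnaire item and one supporting analysis. The planned 60 is unchanged. The downside is that workers on six caseloads are not recruited, which may slow accrual slightly. Because the service has several branches and all PGAP sessions are held online, coaches can still be assigned to participants from elsewhere in the service.

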### Study design

This study is a randomized controlled superiority trial with two parallel groups, in which participants are randomly assigned to an intervention group (PGAP intervention) or a waiting-list control group (care as usual) with an allocation ratio of 1:1. An OP (CH), insurance physician (SV), and the director of an OHS (HZ) were involved in the development in this protocol and study design. They have extensive experience with workers with health problems and know a lot about the practice of OPs and OH practitioners. Besides, the developers of PGAP, who have a lot of experience with PGAP and studying the effects of PGAP were consulted for advice. The design and different measurements of this study are presented in Fig. 1. The schedule of enrollment, interventions, and assessments are presented in Table 1.

**Fig. 1 Fig1:**
[figure not shown]
PGAP study flow-chart

**Table 1 Tab1:**
[figure not shown]
Schedule of enrollment, interventions, and assessments

### Participants

Persons are eligible for inclusion if they are workers between 18 and 65 years old. To participate, persons have to be on sick leave for at least 3 weeks or have frequent spells of sick leave, defined as 3 or more times a year. Eligible participants need to be able to speak, read and write in Dutch and need to be in paid employment. They are eligible if they experience functional limitations associated with their mental or physical health problems. In addition, they need to have at least one cognition or perception that can limit work participation; catastrophizing thoughts, perceived injustice, fear-avoidance beliefs, or disability beliefs. Whether the workers have these limiting cognitions and perceptions will be indicated by a score above the threshold on different questionnaires which are described in the outcome measures section of this protocol.

### Sample size

Results of power analysis (*α* = .80, *p* < .05) show that at least 25 participants per group are needed to detect a change in post score of 2.4 points on the primary outcome catastrophizing as measured with the Symptom Catastrophizing Scale (SCS; SD = 3.0). The standard deviation of 3.0 points and the change of 2.4 points on the SCS are based on a previous study on the effects of PGAP by Moore et al. [23]. On the basis of previous research on the effect of PGAP, we expect that we will lose 15% of the participants in follow-up [24]. Therefore we aim to randomize at least 60 participants; 30 in the control group and 30 in the intervention group.

### Recruitment procedure

Participants will be recruited by OPs and OH practitioners from a large national OHS in the Netherlands. The OP or OH practitioner assesses whether the worker is possibly eligible for participation. The OP or OH practitioner assesses (1) whether the worker is on long-term or frequent sick leave, (2) whether he or she experiences functional limitations associated with his or her mental or physical complaints, and (3) whether the worker possibly has cognitions or perceptions that may limit workability or work participation. When the OP or OH practitioner thinks PGAP is a suitable intervention for the worker, he or she asks if the worker is interested in participating in the PGAP project. The OP or OH practitioner gives the participant a leaflet with information about the project. If the worker is interested and gives permission, the OP or OH practitioner will send the contact details of the worker to the researchers. Next, the researchers send the worker the information letter about the PGAP project and an informed consent form. Workers will also be able to ask questions about the PGAP project during an online meeting with one of the researchers and will watch an introduction video about PGAP. If the worker is not interested in participation, the OP or OH practitioner asks whether the worker wants to provide the reason for this, but the worker is not obliged to provide a reason. When the worker is interested, has signed the informed consent form, and has sent it to the researcher, he or she receives the first screening questionnaire which can be completed online. With the screening questionnaire, we will assess whether the worker really has limiting cognitions and perceptions. Only then, the worker meets the inclusion criteria and can participate in PGAP. The screening questionnaire will also be used as the T0 measurement.

In order to motivate workers to participate in this study and to remain participants throughout the study, all participants will have the opportunity to participate in PGAP without costs and all participants will receive a gift card of 20 euros after finishing the study.

